## **6.2 Randomisation, blinding and treatment allocation**

After completion of preoperative chemotherapy and signing informed consent at the outpatient clinic, participants will be randomized by means of an online random number generator, stratified by centre. Randomization will be performed by the coordinating investigator and directly provided to the participating centres. The data-analyst will be blinded for the procedure.

## **6.3 Study procedures**

Patient will undergo one of the following surgical procedures:

Laparoscopic gastrectomy: n= 105

Open gastrectomy: n= 105

Additional measures:

| Pre-operative                                                        | Post-operative                                                                                                                                                                                |
|----------------------------------------------------------------------|-----------------------------------------------------------------------------------------------------------------------------------------------------------------------------------------------|
| Blood sample for biobanking and baseline                             | Blood 6h postoperatively and on postoperative day 2.                                                                                                                                          |
|                                                                      | VAS-score for pain and vital signs during hospital stay                                                                                                                                       |
| QoL assessment
Groningen Frailty Indicator
Score
SNAQ score | QoL assessment and VAS scores for pain at 6 weeks, 3, 6, 9 months and 1-5 year after surgery.
Productivity assessment (SF-HLQ questionnaire)
Health care use (questionnaire appendix 3) |

#### 6.4 Withdrawal of individual subjects

Subjects can leave the study at any time for any reason if they wish to do so without any consequences. The investigator can decide to withdraw a subject from the study for urgent medical reasons. Subjects not undergoing the allocated treatment (e.g. intraoperatively unresectable tumor) due to medical reasons will not be withdrawn from the study unless the subject requests to do so. Participants will be analysed in an intention-to-treat model.

#### 6.5 Replacement of individual subjects after withdrawal

Study participants will be replaced by newly recruited and randomized subjects in case of withdrawal before surgery, in order to meet the sample size requirement. Patients who withdraw after hospital discharge will not be replaced.

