## 3. STUDY DESIGN

### *Design*

The study design is a non-blinded multicenter prospectively randomized controlled trial. Analysis will take place on an intention-to-treat basis.

The participating patients are randomized for one of the 2 treatment arms. The experimental arm consists of the laparoscopic approach, whereas the control arm is the comparison to the conventional surgery, consisting of the open approach (figure 2).

[figure not shown]

**Figure 2: Treatment allocation. Based on tumor location patients will undergo either distal or total gastrectomy, according to the Dutch gastric cancer guidelines.**

*Duration*

The duration of the study will be 3 years of inclusion + 5 years follow-up.

*Setting*

This study takes place in a hospital setting. Recruitment of patients will occur at the outpatient clinic. Participating patients will receive either laparoscopic (experimental arm) or open (conventional surgery) gastrectomy at the surgical theater. Postoperative care takes place at the surgical ward of the participating hospitals.

*Quality of Life*

The regular postoperative care for patients that undergo a gastrectomy for gastric cancer consists of an annual outpatient visit for the follow-up period of 5 years. This visit is used to check for signs of recurrence of disease and metastases, as well as long term complications. In addition to this standard care quality of life questionnaires will be sent to the patients home address to check the long term effects of the surgical procedure.

*Cost-effectiveness*

To evaluate the cost-effectiveness of both study procedures, an important secondary study parameter, medical costs will be related to productivity and quality of life. All medical costs related to the study procedure will be collected up to five years after the operation. Quality of life will be measured as mentioned above. Furthermore, study participants will be asked to fill in the questionnaire SF-HLQ to measure the productivity after surgery (appendix 3). An expert from the UMC Utrecht Julius Center will do the final cost-effectiveness analysis.

*Blood samples*

Blood samples will be drawn at baseline, 6 hours postoperatively and on postoperative day 2. The aim is to monitor the CRP, leukocytes, haemoglobin and a panel of interleukines production to obtain an indication of the inflammatory response during the early postoperative course.

*Biobanking*

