#### 6.6 Follow-up of subjects withdrawn from treatment

Patients who withdraw from the study will be followed-up until moment of withdrawal.

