#### 6.7 Inclusion of additional patients

For subjects not undergoing the allocated treatment (e.g. unresectable tumor) due to medical reasons, additional subjects will be included in the study to reach the calculated sample size (n=210).

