## 8. STATISTICAL ANALYSIS

Subjects will be analysed by means of an intention-to-treat model.

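### Sections 6.5 and 6.6 together undercut the stated intention-to-treat analysis: patients who withdraw before surgery are replaced and leave no recorded hospital stay

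*Protocol*

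**What the plan says.** - **Analysis principle.** Protocol section 3 (Design): "Analysis will take place on an intention-to-treat basis". Section 6.4: "Participants will be analysed in an intention-to-treat model". Section 8: "Subjects will be analysed by means of an intention-to-treat model".
- **Knowledge of allocation.** Section 3: "The study design is a non-blinded multicenter prospectively randomized controlled trial". Section 6.2: "After completion of preoperative chemotherapy and signing informed consent at the outpatient clinic, participants will be randomized". The same section sends the result straight to the centres. The arm is therefore known before the operation.
- **Withdrawal before surgery.** Section 6.5: "Study participants will be replaced by newly recruited and randomized subjects in case of withdrawal before surgery". The reason given is to meet the sample size. Withdrawal after discharge leads to no replacement. Withdrawal between surgery and discharge is not mentioned.
- **Data after withdrawal.** Section 6.6: "Patients who withdraw from the study will be followed-up until moment of withdrawal".
- **Not treated as allocated.** Section 6.4 keeps patients who miss the allocated operation for medical reasons in the study unless they ask to leave. For them, section 6.7 says that "additional subjects will be included in the study to reach the calculated sample size (n=210").
- **Primary outcome and planned size.** Postoperative hospital stay in days (6.1.1), compared by Mann-Whitney U (8.1). Section 4.4 plans for 14 versus 18 days with 105 + 105 patients, and gives no allowance for loss.

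**The concern.** Intention-to-treat protects the comparison only if patients are analysed whatever they do after learning their arm. Here a patient can learn the arm, leave before surgery, stop counting towards 210 and leave no value for the primary outcome. The Summary and Introduction say that more than five Dutch centres already perform laparoscopic gastrectomy routinely, so a patient allocated to open surgery might leave in order to obtain it. If such leavers are fitter than those who stay, the open arm is left with longer stays and laparoscopy looks better than it is.

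Sections 6.5 and 6.6 govern recruitment and data collection. A statistical analysis plan can define the analysis set, but it cannot recover dates that the protocol stopped collecting.

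**Working it through.** **1. The planned number.** Section 4.4 gives a difference of 4 days, alpha 0.05 and power 0.80, but no SD and no sidedness. From n = 2(z₁₋α/₂ + z₁₋β)²σ²/Δ² with n = 105 and a two-sided test, σ = 4 / (2.80 × √(2/105)) ≈ 10.3 days. With a one-sided test it is about 11.7. As the SD is unstated, 210 can be neither confirmed nor refuted. Replacement and top-up stand in for an allowance for loss.

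**2. Where the outcome is lost.** For a patient who withdraws before surgery, 6.5 recruits a substitute and 6.6 closes data collection before the primary outcome can exist. No section says how that patient is analysed. Three sections say intention-to-treat. Followed as written, the data available for the primary test are those of patients who reached surgery.

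**3. What replacement does.** Replacements are newly randomised, not placed in the vacated arm. If a fraction w of the open arm alone leaves, reaching 210 operated patients takes 210/(1 − w/2) randomised:

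- w = 5%: 210/0.975 ≈ 215
- w = 10%: 210/0.95 ≈ 221
- w = 15%: 210/0.925 ≈ 227, of whom about 227/2 × 0.85 ≈ 97 are operated open patients

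The total is restored; the missing stays are not.

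**4. Size of the bias (every input below is assumed).** There is no true effect; stay is lognormal with median 16 days (midway between 14 and 18) and log-SD σ = 0.635. Leavers come from the fitter half, and fitness correlates with shorter log-stay at ρ = 0.2 to 0.5. The mean of a standard normal above zero is 0.798, so losing a fraction w lowers mean fitness among those left by 0.798·w/(1 − w): 0.0163 at 2%, 0.0887 at 10%, 0.1408 at 15%. The spurious gain is about 16 × (exp(ρσ × difference between arms) − 1).

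| Withdrawal lap / open | ρ | Calculation | Gain (days) |
|---|---|---|---|
| 2% / 10% | 0.5 | 16 × (exp(0.3175 × 0.0724) − 1) | 0.37 |
| 2% / 10% | 0.2 | 16 × (exp(0.127 × 0.0724) − 1) | 0.15 |
| 0% / 15% | 0.5 | 16 × (exp(0.3175 × 0.1408) − 1) | 0.73 |
| 0% / 15% | 0.2 | 16 × (exp(0.127 × 0.1408) − 1) | 0.29 |

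Simulation with the Mann-Whitney test (2,500 to 4,000 runs per scenario) agrees within simulation error: about 0.4, 0.1, 0.8 and 0.3 day in the same order.

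False positives favouring laparoscopy (nominal 2.5%) are about 4% to 5% at 2% / 10% and about 7% to 8% at 0% / 15%, both with ρ = 0.5. With ρ = 0.2, the 0% / 15% case gives a total two-sided error of 5.9%. At 2% / 5% with ρ = 0.5 the gain is 0.1 day and the two-sided error 5.0%. Equal withdrawal of 5% in both arms gives no bias. Replacing within the arm or by fresh randomisation gives nearly the same results.

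A cruder check needs no distribution. If leavers would have stayed D days less than those who remain, the open-arm mean is overstated by w × D: 5% × 3 = 0.15 day, 15% × 5 = 0.75 day. An assumed D of 8 days would take it to 15% × 8 = 1.2 days.

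**5. Section 6.7.** If a fraction u of patients is not treated as allocated, reaching 210 treated patients needs 210/(1 − u) randomised, rounded up: 222 at 5%, 234 at 10%, 248 at 15%. All remain in the study under 6.4, so the intention-to-treat set exceeds 210 by a number that the protocol does not state.

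**The case against.** **Intention-to-treat is stated three times, and nothing says that a replaced patient is excluded.** This stands. A reader might infer that the protocol removes these patients from the analysis set; it does not say so. The exclusion follows in practice because no outcome is collected, and the handling of such patients may be set out in an analysis plan that is not shown. The data collection rule in 6.6 remains a protocol matter.

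**Replacement is harmless in itself.** This also stands. A reader might infer that leavers are swapped one for one within an arm, or that abolishing replacement would cure the problem. Substitutes are randomised afresh, and a leaver has no recorded stay whether or not someone is recruited in addition. Deleting the rule would leave the same selection and a smaller n.

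**Section 6.7 does not breach intention-to-treat.** Correct. A reader might take the top-up as a second contradiction, but 6.4 keeps the untreated patients in the study and 6.7 only adds others. What remains is the unclear meaning of 210.

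**The bias may be negligible.** Patients have a week to consider before consenting (9.2), which may limit allocation-driven exits. That open-arm patients will leave to seek laparoscopy is conjecture. With similar withdrawal in both arms, or a weak link between fitness and stay, little happens. Continued collection also depends on permission from someone who has the right to leave. All of this limits the size and certainty of the concern, but does not remove the gap.

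**Conclusion.** The point holds for 6.5 and 6.6 taken together: as written, they turn the promised intention-to-treat comparison of the primary outcome into one of patients who reached surgery, in a trial where the arm is known beforehand.

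The size is uncertain. The protocol gives no withdrawal rate, no SD, and nothing on who would leave. Under the simulated assumptions the spurious gain is about 0.1 to 0.8 day, or 2.5% to 20% of the planned 4 days (0.1/4 and 0.8/4). The error rate rises clearly only under one-sided withdrawal of 15% with a correlation of 0.5. These figures show what the rule would permit, not a bias that has been shown to exist.

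The change is worth making because it is cheap and the lost dates may not be recoverable later. The evidence does not support calling it critical.

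**What to change.** - **Sections 6.5 and 6.7:** keep the extra recruitment, but state that no randomised patient is removed from the intention-to-treat set and that the randomised total may exceed 210.
- **Section 6.6 and the consent form:** ask patients who withdraw for permission to take operation date, discharge date and vital status from the hospital record, and analyse them in the allocated arm.
- **Section 6.5:** cover withdrawal between surgery and discharge, the period in which the primary outcome accrues.
- **Reporting:** give pre-surgery withdrawals by arm with reasons.
- **Analysis:** add a sensitivity analysis for stays still missing, including those of patients who refuse permission or never have an operation.

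The cost is a few sentences in 6.5 to 6.7, one consent line, a little record review, and an analysed n that may differ from 105 + 105.

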#### 6.6 Follow-up of subjects withdrawn from treatment

Patients who withdraw from the study will be followed-up until moment of withdrawal.

#### 6.7 Inclusion of additional patients

For subjects not undergoing the allocated treatment (e.g. unresectable tumor) due to medical reasons, additional subjects will be included in the study to reach the calculated sample size (n=210).

## **7. SAFETY REPORTING**

### **7.1 Section 10 WMO event**

In accordance to section 10, subsection 1, of the WMO, the investigator will inform the subjects and the reviewing accredited METC if anything occurs, on the basis of which it appears that the disadvantages of participation may be significantly greater than was foreseen in the research proposal. The study will be suspended pending further review by the accredited METC, except insofar as suspension would jeopardise the subjects' health. The investigator will take care that all subjects are kept informed.

### **7.2 AEs, SAEs and SUSARs**

#### **7.2.1 Adverse events (AEs)**

Adverse events are defined as any undesirable experience occurring to a subject during the study, whether or not considered related to allocated surgery. All adverse events of a modified Clavien-Dindo classification grade 2 and higher and reported spontaneously by the subject or observed by the investigator or his staff, will be recorded starting from the day of surgery until the start of adjuvant therapy or up to 3 months after surgery. Events occurring outside of this period are not expected to be related to the study intervention, but more likely to (neo)adjuvant treatment or disease progression.

#### **7.2.2 Serious adverse events (SAEs)**

A serious adverse event is any untoward medical occurrence or effect that at any dose:

- results in death;
- is life threatening (at the time of the event);
- requires hospitalisation or prolongation of existing inpatients' hospitalisation;
- results in persistent or significant disability or incapacity;
- is a congenital anomaly or birth defect;
- Any other important medical event that may not result in death, be life threatening, or require hospitalization, may be considered a serious adverse experience when, based upon appropriate medical judgement, the event may jeopardize the subject or may require an intervention to prevent one of the outcomes listed above.

The SAE's that will be reported during this study are SAE's occurring starting from the day of surgery until the start of adjuvant therapy or up to 3 months after surgery.

Events occurring outside of this period are not expected to be related to the study intervention, but more likely to (neo)adjuvant treatment or disease progression.

The local coordinating investigator per centre is responsible for reporting the SAEs to the sponsor.

The sponsor will report the SAEs through the web portal *ToetsingOnline* to the accredited METC that approved the protocol, within 3 months after the sponsor has first knowledge of the serious adverse reactions by means of a periodical overview

SAEs that result in death should be reported expedited. The expedited reporting will occur not later than 7 days after the responsible investigator has first knowledge of the adverse reaction. This is for a preliminary report with another 8 days for completion of the report.

### **7.2.3 Suspected unexpected serious adverse reactions (SUSARs)**

Not applicable.

## **7.3 Annual safety report**

Not applicable.

## **7.4 Follow-up of adverse events**

All AEs will be followed until they have abated, or until a stable situation has been reached. Depending on the event, follow up may require additional tests or medical procedures as indicated, and/or referral to the general physician or a medical specialist.

SAEs need to be reported till end of study within the Netherlands, as defined in the protocol

## **7.5 Data Safety Monitoring Board (DSMB)**

The stop-criteria are:

- <70% complete resection without tumor residual in the proximal or distal surgical resection plane (R0) in one or both arms,
- >50% less than 10 lymph node harvested in one or both arms.

A data safety monitoring board will be assigned to evaluate the outcomes at 105 patients.

A DSMB is established to perform ongoing safety surveillance and to perform interim analyses on the safety data. This committee is an independent committee, which is composed of (names will be determined at a later stage).

None of the members have a conflict of interest with the sponsor of the study.

Criteria on which the DSMB may decide to terminate the trial prematurely:

- Clear evidence of benefit of laparoscopic gastrectomy
- Clear evidence of harm of laparoscopic gastrectomy
- External evidence, such as other trials or published data, not available during the start of this trial.

The advice(s) of the DSMB will only be sent to the sponsor of the study. Should the sponsor decide not to fully implement the advice of the DSMB, the sponsor will send the advice to the reviewing METC, including a note to substantiate why (part of) the advice of the DSMB will not be followed.

## 8. STATISTICAL ANALYSIS

Subjects will be analysed by means of an intention-to-treat model.

### 8.1 Primary study parameter

The primary outcome measure is postoperative hospital stay. This variable is expected to have a non-Gaussian distribution and will therefore be analysed by means of a Mann-Whitney-U test in univariate analysis.

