### Surgery

In 1993, a laparoscopic approach to the treatment of gastric cancer was reported for the first time (5). Ever since, laparoscopic techniques and surgical experience have improved, allowing complex laparoscopic procedures such as laparoscopic distal gastrectomy and laparoscopic total gastrectomy to be performed. Systematic reviews and meta-analyses have shown an advantage in short-term outcomes of laparoscopic distal gastrectomy compared with open distal gastrectomy (6-11). Our recent meta-analysis, containing 8 comparative cohort studies, shows similar advantages for laparoscopic total gastrectomy (12).

Laparoscopic total gastrectomy was associated with a reduction of intra-operative blood loss (weighted mean difference 228 ml; 95% c.i. 311-144;  $p < 0.001$ ), a reduced risk at postoperative complications (risk ratio 0.51; 95% c.i. 0.33-0.77), and admission time was shortened from 18 to 14 days (figure 1, weighted mean difference 4 days; 95% c.i. 1.3-6.5;  $p < 0.001$ ). These benefits were at the cost of a prolonged duration of surgery (weighted mean difference 56 minutes (95% c.i. 25-86);  $p < 0.001$ ). In hospital mortality rates were comparable for the laparoscopic (1%) and open approach (2%) (risk ratio 0.68; 95% c.i. 0.20-2.36).

[figure not shown]

**Figure 1: Postoperative hospital stay was evaluated in 7 out of 8 comparative cohort studies in our meta-analysis. Hospital stay was shortened from 18 days after open gastrectomy to 14 days after laparoscopic gastrectomy.**

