| Postoperative bleeding           | 1 (4%)                                     | 2 (7%)                                             | 0.690          |
| Anastomotic leakage              | 11 (46%)                                   | 5 (17%)                                            | 0.020          |
| Anastomotic stricture            | 7 (29%)                                    | 6 (20%)                                            | 0.434          |
| Dilated                          | 7 (29%)                                    | 6 (20%)                                            | 0.434          |
| Stent                            | 6 (25%)                                    | 2 (7%)                                             | 0.590          |
| Chylothorax                      | 1 (4%)                                     | 1 (3%)                                             | 0.872          |
| Postoperative hospital stay (d)* | 25 (7-188)                                 | 12 (7-53)                                          | 0.003          |
| Intensive care stay (d)*         | 5 (0-57)                                   | 1 (0-26)                                           | 0.020          |
| Resected lymphnodes (n)*         | 16 (3-33)                                  | 19 (2-53)                                          | 0.376          |
| Tumor positive (n)*              | 3 (0-15)                                   | 1 (0-33)                                           | 0.927          |
| R0 resection                     | 22 (92%)                                   | 28 (93%)                                           | 0.816          |
| Mortality                        |                                            |                                                    |                |
| 30-day mortality                 | 1 (4.2%)                                   | 1 (3.3%)                                           | 0.087          |
| 60-day mortality                 | 4 (16.7%)                                  | 2 (6.7%)                                           | 0.245          |

**Table 1: Intraoperative and Postoperative Outcomes****\*Results presented as medians (min-max)****Reasons for conversion: tumor ingrowth in surrounding structures (6x), arterial bleeding (1x), venous bleeding (1). R0 resection: proximal and distal resection margin.**

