### 4.4 Sample size calculation

The primary outcome parameter is postoperative hospital stay. A recent meta-analysis has shown that laparoscopic procedure shortens the median hospital stay with 4 days (12).

Hospital stay after laparoscopic gastrectomy: 14 days

Hospital stay after open gastrectomy: 18 days

Significance level ( $\alpha$ ) = 0.05

Power ( $1-\beta$ ) = 0.80

Sample size:

Total number of 210 participants:

- Laparoscopic gastrectomy (experimental arm) = 105
- Open gastrectomy (conventional surgery) = 105

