## **6. METHODS**

### **6.1 Study parameters/endpoints**

#### **6.1.1 Main study parameter/endpoint**

- Postoperative hospital stay (days)

The following criteria have to be met:

- Adequate pain control with oral pain medication

- Started with mobilisation
- Adequate intake according to nutritional demand and being independent of supplementary intravenous fluids

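### The primary Mann-Whitney test on postoperative days does not separate discharge alive from in-hospital death, so an early death can take a favourable rank

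*Protocol*

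**What the plan says.** Protocol section 6.1.1 names postoperative hospital stay in days as the main endpoint. It adds "The following criteria have to be met" and lists oral pain control, mobilisation and adequate intake. It does not say whether these are conditions for discharge, for the end of the counted stay, or for a patient to have a valid value.

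Section 8 sets the analysis principle: "Subjects will be analysed by means of an intention-to-treat model". Section 8.1 sets the test: "This variable is expected to have a non-Gaussian distribution and will therefore be analysed by means of a Mann-Whitney-U test in univariate analysis". Mortality and readmission are separate secondary endpoints in 6.1.2. Neither 6.1.1 nor 8.1 says how an in-hospital death enters the primary comparison.

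**The concern.** A rank test on days treats fewer days as better. That is right only if leaving hospital means recovering. A patient who dies on day 4 also has few days. Entered as a 4-day stay, that patient ranks ahead of nearly everyone: Table 1 in section 1 gives a shortest stay of 7 days in both groups.

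For early deaths the endpoint can therefore move in the wrong direction. An excess of early deaths in one arm adds favourable ranks to that arm. The text also pulls two ways: intention to treat requires a value for every patient, while 6.1.1 attaches criteria that a patient who dies in hospital may never meet. Raw day of death, exclusion and worst rank are all compatible with the wording, and they can give different primary results.

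**Working it through.** **Inputs from the protocol.** Section 4.4: 14 days laparoscopic, 18 days open, alpha 0.05 (taken as two-sided), power 0.80, 105 per arm. Section 1: in-hospital mortality 1% laparoscopic, 2% open (meta-analysis). Table 1: 30-day mortality 1/30 laparoscopic, 1/24 open; 60-day mortality 2/30 and 4/24.

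**Spread.** The protocol gives no SD, so 210 cannot be reproduced from its own inputs. Back-solving with the normal approximation:

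SD = 4 / [(1.960 + 0.842) × √(2/105)] = 4 / (2.802 × 0.1380) ≈ 10.3 days.

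For the rank test I assume lognormal stay with medians 14 and 18 and log-SD 0.635, chosen to give about 80% power without deaths. Spread and death timing are assumptions, not protocol figures.

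**What one death does to the test.** With n = 105 per arm, Var(U) = n²(2n + 1)/12 = 105² × 211/12 = 193,856, so SD(U) = 440.3.
- Moving one patient from a neutral rank to the best rank shifts z by 0.5 × 105/440.3 = 0.12.
- Moving one patient from best to worst rank shifts z by 105/440.3 = 0.24.
- At 1% against 2% the expected excess is 0.01 × 105 ≈ 1 death, in the open arm.
- At 5% against 2% it is 0.03 × 105 ≈ 3 deaths, a best-to-worst swing of about 3 × 0.24 = 0.72 in z.

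**Simulation.** Probability of a significant laparoscopic benefit, 3,000 to 10,000 trials per row. Ranges are across repeat runs; Monte Carlo error is under one point.

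| In-hospital deaths, lap/open | Assumed days of death | Raw days | Death ranked worst |
|---|---|---|---|
| none | – | about 80% | about 80% |
| 1% / 2% (cited) | 2–14 | 76% | 81% |
| 1% / 2% (cited) | 7–30 | 79% | 81% |
| 5% / 2% (illustrative) | 2–14 | 82–83% | 58–59% |
| 5% / 2% (illustrative) | 2–30 | 76–78% | 59% |
| 5% / 2% (illustrative) | 7–60 | 68–70% | 59% |

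With log-SD 0.6 and every death in the first week, the 1%/2% row becomes 79% against 84%, so the size does not hinge on the exact spread.

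**Reading the 5%/2% row.** The raw-days figure of 83% is only slightly above the no-death 80%. Most of the gap arises because worst-rank scoring counts the excess deaths against the arm, while raw days do not and give it slight credit.

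**No true difference in stay.** At 5%/2%, the chance of a false result favouring laparoscopy (nominal 2.5%) is 4.4% on raw days with deaths on days 2–14, and 5.6% with deaths on days 1–7 and log-SD 0.6. With death ranked worst it is about 1% in both settings.

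**The case against.** **The protocol never says that a death counts as a short stay.** Correct. A reader might infer that it does, but section 8.1 names only the test, and the criteria in 6.1.1 point away from treating death as a completed stay. A rule may also stand in a statistical analysis plan that is not shown, and its absence here would not by itself be an error. What remains is that the endpoint definition belongs to the protocol, and 6.1.1 does not say what ends a stay.

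**Table 1 might suggest a large distortion.** A reader could take its 60-day mortality (6.7% laparoscopic, 16.7% open), treat every death as early and in hospital, and obtain 33% on raw days against 93% with death ranked worst. The table does not support this. By day 30 it shows one death per group, so three of the four open deaths and one of the two laparoscopic deaths came later. With the 30-day deaths placed on days 7–30 and the rest on days 31–60, all assumed in hospital, the two analyses agree at about 93–94%.

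**The bias might be thought to favour the experimental arm.** Every mortality figure in the protocol is lower for laparoscopy, so at the cited rates the literal reading works slightly against it. The 5%/2% scenario is an assumption.

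**Deaths would not be hidden.** This stands. Mortality is a secondary endpoint, fatal serious adverse events are reported expedited (7.2.2), and the DSMB may stop for harm (7.5). That limits the damage but does not settle the primary result.

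**Readmitted and unresected patients.** A reader might extend the point to both. Readmission has its own secondary endpoint. For unresected patients section 6.4 says "Subjects not undergoing the allocated treatment (e.g. intraoperatively unresectable tumor) due to medical reasons will not be withdrawn from the study"; retaining them is proper intention to treat, and randomisation should balance tumour resectability. No differential effect is shown, so ranking them worst would be a preference, not a correction.

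**Conclusion.** The point stands in a limited form. Sections 6.1.1, 8 and 8.1 together fix a rank comparison of raw days without separating discharge alive from death. Read literally, this favours early in-hospital deaths only. At the cited 1% against 2% the cost is about 2 to 5 points of power, against laparoscopy. A material effect needs an imbalance of several early deaths: about 83% against 58% for an assumed 5%/2% on days 2–14, and a smaller gap if deaths come later. These figures rest on an assumed lognormal stay, an assumed spread and assumed death timing.

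This is worth settling before analysis because the remedy is nearly free. It does not invalidate the design, and the documents do not show that the trial would reward the arm with more deaths at the mortality it expects.

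**What to change.** - **Section 6.1.1:** define the endpoint as days from surgery to discharge alive, and state how the listed recovery criteria relate to discharge, so that every randomised patient's value follows from the text.
- **Section 8.1:** give in-hospital deaths the worst rank, longer than any observed stay, in the primary Mann-Whitney test. Keep raw days as a sensitivity analysis.
- **Optional:** report total hospital days including readmissions as a supporting analysis.

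The activity table in section 3 already collects stay, readmissions and mortality, so no data or patients are added. The cost is a few sentences, carried into the statistical analysis plan. The downside is one of interpretation: the primary result becomes a rank comparison of stay that includes death, not of days alone. Discharge alive with death as a competing event is another defensible choice; what matters is that one rule is fixed in advance.
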